**Figure 1 F1:**
[figure not shown]
Flowchart. CRP = cardiovascular rehabilitation program.

### Sample characterization

2.5

For the sample characterization, the volunteers’ medical records are going to be analyzed in order to identify information about their age, gender, clinical diagnoses, cardiovascular risk factors, and associated pathologies (musculoskeletal, neurological, pulmonary, and/or metabolic disfunction).

For the volunteers’ risk stratification according to the protocols selected in this study, their clinical history and the results of their last laboratory and complementary examinations related to the cardiovascular system are going to be extracted from their medical records.

For the clinical history, information about the number of cardiorespiratory arrests, hospital days, and complications during the hospital days or after procedures are going to be considered. For the laboratory tests, blood glucose, triglycerides, total cholesterol, high-density lipoprotein (HDL)-cholesterol, and low-density lipoprotein (LDL)-cholesterol are going to be considered. For the complementary examinations, cardiovascular examinations, such as exercise stress test, echocardiogram, Holter, catheterization, myocardial scintigraph, electrocardiogram, and coronary angiotomography are going to be considered.

We are also going to measure the height in orthostatic position with a stadiometer (Sanny, Personal Caprice, Brazil) and body mass with a digital balance (Balmak, Premium, Bk–200Fa, Brazil), in order to calculate the body mass index (BMI).^[40]^

### Cardiac risk stratification

2.6

For the volunteers’ cardiac risk stratification, 8 protocols reported by Silva et al^[39]^ are going to be used. The patients are going to be classified in accordance to each protocol, considering their tests and evaluation, as less, moderate, and high risk, and if they have 1 characteristic considered as higher cardiovascular risk, they will be classified on this category. Furthermore, if the patients do not fulfill the criteria for the stratification in any of the protocols, they are going to be classified as “impossible to classify.”

The American Heart Association (AHA)^[41]^ protocol classifies the patients according to risk classes (A, B, C, D), considering the presence of symptoms or CVD, respiratory rate, and the exercise stress test. The patients classified as A risk class are going to be considered as less risk, B risk class are going to be considered as moderate risk, and C risk class are going to be considered as high risk. According to AHA, patients classified as C risk class should not participate in CRP.

### Evaluation of clinical parameters

2.7

In relation to clinical parameters, we are going to evaluate some of them related to the cardiorespiratory system and autonomic modulation, such as blood pressure (BP), heart rate (HR), oxygen saturation (SatO_2_), respiratory rate (f), maximal inspiratory pressure (MIP), maximal expiratory pressure (MEP), peak expiratory flow (PEF), forced expiratory volume in 1 second (FEV1), forced vital capacity (FVC), FEV1/FVC ratio, and HRV.

#### Cardiovascular parameters

2.7.1

The blood pressure measure is going to be done as an indirect form, with an stethoscope (Littmann, St Paul, MN) and aneroid sphygmomanometer (Welch Allyn, Tycos, NY).^[42]^ The HR is going to be verified using a cardiac monitor Polar (Polar Electro OY, V800, Finland) and its value is going to be obtained through the average of the 5 to 20 minutes of the RR intervals.

#### Respiratory parameters

2.7.2

For the oxygen saturation, we are going to use a pulse oximeter (Rossmax Innotek Corp, SB220, Taiwan), which is going to be fixed on the index finger of each volunteer. The respiratory rate is going to be measured individually through the number of the respiratory cycles performed for one minute.

The MIP and MEP are going to be measured with an analogical manovacuometer (Murenas, 71001WTB CL1.6, Brasil), calibrated in 300 cmH_2_O.^[43,44]^ To measure the spirometry values, we are going to use a portable spirometry (MIR Medical International Research, Spirobank II Advanced, Itália). Through the time-volume curve, the peak expiratory flor (PEF), FEV1, FVC, and FEV1/FVC^[45]^ are going to be obtained.

#### Autonomic modulation

2.7.3

The autonomic modulation is going to be evaluated through the HRV analysis. For this analysis, the HR will be recorded beat-to-beat in a quiet room, with temperature controlled between 21° and 24° C and air relative humidity between 40% and 60%. The data collection is going to be done individually and the patients remain at rest in an orthostatic position for 30 minutes. The patients are going to be oriented to not consuming stimulant substances of the ANS such as alcoholic drinks, coffee, tea, soda, and chocolate for 24 hours before HRV analysis.

A heart rate monitor Polar RS800CX (Polar Electro OY, V800, Finland) is going to be used for HR record, and the data recorded are going to be transferred to the computer through the Polar Flow web service (https://flow.polar.com/).

For the data analysis, we are going to use 1000 consecutive RR intervals, after a digital filtering complemented by a manual filtering, to eliminate ectopic, premature, and artifacts beats, and only series with more than 95% of heart sinus beat are going to be included in the study.

Linear indices of HRV in the time and frequency domain are going to be used for HRV analysis. In the time domain, RMSSD (root mean square to the successive differences between each heartbeat) and SDNN (standard deviation of all normal RR intervals) are going to be calculated.^[46]^ In the frequency domain, the spectral components of low frequency (LF: 0.04–0.15 Hz) and high frequency (HF: 0.15–0.40 Hz) are going to be evaluated, in milliseconds squared (ms^2^) and normalized units (nu), and also the relation between LF and HF components (LF/HF). The spectral analyses are going to be calculated using the algorithm of Fast Fourier transform.^[46]^

In addition, the HRV is going to be also calculated through the quantitative analysis of Poincaré Plot, considering the following indices: SD1 (standard deviation of distances of diagonal points), SD2 (standard deviation of the distances from points to lines), and finally the SD1/SD2 that describes the ratio between short and long variations of RR intervals.^[46]^

All the HRV indices are going to be obtained using Kubios HRV Standard software – version 3.0.0 (Kubios, Biosignal Analysis and Medical Image Group, Department of Physics, University of Kuopio, Kuopio, Finland).

### Physical parameters

2.8

For analysis of physical parameters, the MIR, MIVC, cardiorespiratory fitness, and physical activity level are going to be measured.

#### Maximum isometric voluntary contraction (MIVC)

2.8.1

The maximal MS is going to be evaluated using a MIVC, performed at the isokinetic dynamometer (Biodex system 4 Pro; New York).^[47]^ Before the beginning of the test, the equipment is going to be calibrated and the patients positioned with individual measures, which are going to be maintained for all moments. The equipment has bands that are going to be fixed on the patients in the trunk, hip, thigh, and distal area of the lower limb (dominant) in order to isolate knee movement. The dominant limb is going to be determined using the following question: “Which leg do you use to kick a ball?”

Before the test, the patients are going to undergo a warm up, consisting of 10 repetitions of concentric contraction of knee flexion-extension at 180°/s throughout the range of motion. The MS is going to be measured throughout the higher torque value obtained among three 5-second repetitions of MIVC at 60° of knee flexion (with 0° corresponding to the maximum extension). To minimize possible fatigue effects, the volunteers are going to have 2 minutes of rest between the test repetitions. Furthermore, the patients are going to be instructed to perform their maximum strength performance.

#### Maximum isometric resistance (MIR)

2.8.2

Maximal isometric muscle resistance is going to be measured using the MIR, performed at the isokinetic dynamometer (Biodex Medical Systems, System 4 Pro, New York) with the same initial orientations of the CIVM.^[48]^

Initially, the patients are going to perform an isotonic warm-up, consisting of 10 knee flexion-extension at a speed of 330°/s, respecting a 90° amplitude. Next, an isometric warm-up is going to be performed, where the patients are going to do 30 seconds of isometric contraction, with an intensity determined according to Borg subjective perception of effort scale (5--6 of intensity).

After 2 minutes of rest, the patients are going to be familiarized with the isometric resistance test. For this, they are going to perform his/her highest perceived effort (according to Borg scale) and to maintain this effort for as long as possible until he/she is unable to maintain muscle contraction. Twenty-five hours after the familiarization, the patients are going to perform the MIR test, which consists of the same familiarization procedures described above.

In order to stimulate the patient, they are going to accompany, in the monitor coupled to the equipment, the force generation line that serves as a visual feedback. In addition, verbal stimuli are going to be given by the measurer during the test.

#### Cardiorespiratory fitness

2.8.3

The cardiorespiratory fitness is going to be evaluated using a 6-minute walking test (6MWT).^[49]^ The patients are going to be encouraged by the measurer during the test to maintain the same walk rhythm until the end of its. The test is going to be performed twice, with 30 minutes of interval between than, and the highest distance performed by the patient is going to be considered for the analysis.

#### Physical activity level

2.8.4

The physical activity level is going to be measured day-by-day using a triaxial accelerometer Actigraph GT3X-BT (ActiGraph, LLC, Pensacola, FL),^[50,51]^ calibrated at 30 Hz. For this, the equipment is going to be positioned on the hip (dominant side) and the patients are going to use it for 7 days, withdrawing only during sleep and water activities.

To be considered a valid day, the individual should remain a period of 10 hours (600 minutes) with the equipment.^[15,50,51]^ After the use, counts activity are going to be analyzed using ActiLife 6.11.8 software (ActiGraph, LLC, Pensacola, FL) with 1 second of epoch, and later, in order to obtain the total in minutes of the time spent in moderate/vigorous physical activity data are going to be re-entered for 60-second epoch. Valid periods are going to be determined subtracting the 24 hours nonvalid periods.^[50]^ These data will provide information related to physical activity level (light, moderate, and high), total steps per day, and total counts per minute, which is estimated based on the following cutoff points: light intensity: 100 to 2019 counts; moderate 2020 to 5998 counts; and vigorous 5999 counts or more.

### Biochemical parameters

2.9

The biochemical parameters IL-6, TNF-alpha, and IL-10 are going to be analyzed. For these, the blood sample (15 mL) is going to be collected with the subjects in fasting for 12 hours. The blood samples are going to be allocated into 2 vacutainer tubes (Becton Dickinson, BD, Juiz de Fora, MG Brazil) containing EDTA for plasma separation, centrifuged at 3500 g during 15 minutes at 4°C, and finally stored at -20°C for further analysis. Cytosines IL-6, IL-10, and TNF-alpha are going to be evaluated using the commercial ELISA kit (R&D Systems, Minneapolis, MN).

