### Eligibility criteria

2.1

Subjects of both genders, with clinical diagnosis of CVD and/or cardiovascular risk factor, able to realize all the evaluations proposed and in accordance to the study procedures are going to be included. Patients with less than 30% of attendance during the period of the protocol are going to be excluded.

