### Study design

2.4

This study is going to be divided in 3 phases. Initially, all the volunteers are going to have their medical records analyzed, and information about the sample characterization and medical examinations are going to be extracted. Two independent blinded and trained measurers are going to realize the risk stratification of the volunteers, using the protocols described into the literature review of Silva et al.^[39]^ Following this, clinical (cardiorespiratory parameters and autonomic modulation), physical [maximum isometric resistance (MIR), maximum isometric voluntary contraction (MIVC), cardiorespiratory fitness, and physical activity level], and biochemical [interleukin (IL)-6, TNF-alpha, and IL-10] parameters are going to be evaluated by a blinded and trained measurer and the subjects are going to be accompanied during 24 sessions of their CRP routines, to register the appearance of their signals and symptoms.

In the second phase, the volunteers are going to realize their normal CRP routines for 6 months. In the third phase, the clinical, physical, and biochemical parameters, described above, are going to be evaluated by a blinded and trained measurer and the volunteers are going to be accompanied for more 24 sessions of their CRP routines, to register the appearance of their signals and symptoms as well.

The description of the phases and the volunteers that will be included in each one of them are reported at Fig. 1.

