### Cardiac rehabilitation program

2.10

The CRP applied to patients who are going to be recruited for the study is composed of the following steps: initial rest, warm-up, resistance, and relaxation phase. The program is performed 3 times a week (Mondays, Wednesdays, and Fridays) totalizing 60 minutes per day, divided as follows: 5 minutes of initial rest, which aims at assessing the BP, HR, and signals and symptoms commonly found in subjects with CVD; 15 minutes of warm-up, performing overall stretching, lower limb exercises, upper limb exercises, and exercises combining both modes; 30 minutes of resistance phase, performing individualized aerobic exercise according to their HR reserve values,^[52]^ using bicycle and treadmill (15 minutes of exercise in each one of these ergometers). In both ergometers, the HR is measured at the 4th and 10th minute, and in bicycle, the BP is also measured. If the patient has some physical restriction, the protocol will be performed in only one of the ergometers (in this case, the HR and BP are measured at the 5th, 15th, and 25th minute); 10 minutes of cooling down, performing a cardiovascular deceleration, for example, with few laps around the room, and finally stay at rest. At the end of this phase, the HR is measured and, if necessary, so is the BP.

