### Data analysis

2.12

The normality of data is going to be analyzed using Shapiro--Wilk test. According to the distribution, the population characteristics will be presented, as mean and standard deviation for parametric distribution and median and interquartile interval for nonparametric distribution.

The relationship between the number of signals and symptoms of the patients and the scale degree of the protocols (1, 2, and 3) is going to be analyzed using Pearson correlation. The concordance degree of each protocol with the number of signals and symptoms are going to be determined using coefficient of intraclass correlation. To determine the efficacy of the risk stratification protocols as soon as clinical, physical, and biochemical parameters to previse signals and symptoms during the CRP, analysis of sensibility and specificity using ROC curve is going to be done. The sensibility, specificity, and predictive value (positive and negative) for the occurrence of events are going to be also registered. If the values of the area on the curve are ≥0.650, it will be considered significative.

To evaluate whether the clinical, physical, and biochemical modifications have influenced in the occurrence of signals and symptoms, the sphericity of the data will be verified by Mauchly test, and if the sphericity be violated, Greenhouse--Geiser correction will be performed. The comparison between the different moments of the clinical (cardiorespiratory parameters and autonomic modulation), physical (maximum isometric endurance, MIVC, cardiorespiratory fitness and physical activity level), and biochemical (IL-6, TNF-alpha, and IL-10) are going to be realized by repeated measures analysis of variance (ANOVA) and the possible differences between the moments will be performed by Bonferroni post-hoc.

The statistical significance difference adopted is going to be fixed in 5% with 95% of confidence interval. The analysis is going to be done on SPSS 15.0 version (SPSS Inc., Chicago, IL).

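### Cytokine plasma kept at -20°C, with the two draws about 8 months apart: a storage or assay-run effect cannot be excluded from the phase 1 to phase 3 change

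*Protocol article*

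**What the plan says.** Section 2.9 (Biochemical parameters) describes the handling of the EDTA plasma in detail, down to centrifuge force, time and temperature. It ends with samples "finally stored at -20°C for further analysis". The assay follows: "Cytosines IL-6, IL-10, and TNF-alpha are going to be evaluated using the commercial ELISA kit". No storage duration, assay date or plate allocation is given.

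Section 2.4 (Study design) sets the timing. The biochemical parameters are measured in phase 1, and then "the subjects are going to be accompanied during 24 sessions of their CRP routines". After that, "In the second phase, the volunteers are going to realize their normal CRP routines for 6 months". Finally, "In the third phase, the clinical, physical, and biochemical parameters, described above, are going to be evaluated by a blinded and trained measurer".

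Section 2.12 (Data analysis) compares the moments: "biochemical (IL-6, TNF-alpha, and IL-10) are going to be realized by repeated measures analysis of variance (ANOVA"). Section 2 describes a single observational cohort, so there is no parallel group.

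**The concern.** With two moments and one cohort, the repeated measures ANOVA of a cytokine is a test of the mean within-patient difference, equivalent to a paired t-test. Anything that shifts all phase 1 values relative to all phase 3 values enters that difference in full. There is no control group in which the same shift would appear and could be subtracted.

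Storage and assay run are two such possible shifts. The stated temperature and the open-ended storage leave both open.

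The third aim asks whether changes in clinical, physical or biochemical parameters influence signals and symptoms. A handling effect in the cytokines would be read as a change over the programme. Under end-of-study assay the direction is known: loss in the older phase 1 samples would hide a true fall or show a false rise. TNF-alpha is one of the main variables named in section 2.2 (Sample size), although the sample size itself rests on rMSSD.

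**Working it through.** The article states no interval between draws and no storage time, so there is no figure of its own to reproduce. The interval follows from its schedule.

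**Inputs from the article**
- Sessions followed between the first draw and phase 2: 24 (section 2.4).
- Frequency: "The program is performed 3 times a week (Mondays, Wednesdays, and Fridays"), section 2.10.
- Phase 2: 6 months, about 26 weeks (section 2.4).
- Attendance floor: "Patients with less than 30% of attendance during the period of the protocol are going to be excluded" (section 2.1).
- Sample size: 44 (section 2.2).

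**Step 1: interval between draws**
- Full attendance, or 24 scheduled sessions: 24/3 = 8 weeks, and 8 + 26 = 34 weeks. In months, 8/52.18 × 12 = 1.84, and 1.84 + 6 = 7.84.
- If 24 attended sessions are required and attendance is 30%: 24/(3 × 0.3) = 26.7 weeks, and 26.7 + 26 = 52.7 weeks. In months, 6.13 + 6 = 12.13.
- In between, on the same condition: 8.3 months at 80% attendance and 9.7 months at 50%.

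**Step 2: what the interval means for the assay**

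| Assay timing (not stated) | Difference in storage time within a patient | What cannot be separated from the programme |
|---|---|---|
| All samples together at the end | 7.8 to 12.1 months | loss during storage |
| Each phase in its own run, after equal delay | about 0 | difference between runs |

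**Step 3: size under end-of-study assay**

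The article gives no loss rate, so the rate L per month is an assumption, and the range includes zero. With g months between draws and no true change, the apparent rise from phase 1 to phase 3 is 1/(1 − L)^g − 1.

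| Assumed L per month | g = 7.84 | g = 12.13 |
|---|---|---|
| 0% | 0% | 0% |
| 0.5% | 4.0% | 6.3% |
| 1% | 8.2% | 13.0% |
| 2% | 17.2% | 27.8% |

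**Step 4: how large a shift would matter with 44 pairs**

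The article gives no SD for cytokine differences, so the shift s is expressed in units of that SD. For a two-sided 5% paired test (normal approximation) with no true change, the chance of a significant result is Φ(s√44 − 1.96) + Φ(−s√44 − 1.96).

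| s | 0 | 0.1 | 0.2 | 0.3 | 0.5 |
|---|---|---|---|---|---|
| False-positive rate | 5% | 10% | 26% | 51% | 91% |

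This applies to a shift from either source, storage or run. It shows how sensitive the comparison is; it does not show that such a shift will occur.

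**The case against.** A reader might infer from the gap that storage time differs by phase. The documents do not support that. It needs both draws to be assayed together, or after unequal delays, and the article does not say when assays are run. Section 2.9 as written also permits assaying each phase after the same short delay.

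A reader might also infer that these cytokines will be lost at -20°C and that false significant changes are therefore likely. No stability data stand in the article. The loss rates in the working are assumed, and at zero the storage effect vanishes. Any false-positive rate is only as good as the shift put into it.

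Three more points stand:
- The 12-month end needs two conditions that the article does not state: that the 24 sessions are attended ones, and that a patient sits at the 30% floor.
- Confounding of phase with run assumes a separate run for each phase. If entry is staggered, one run could contain samples of both phases.
- Batching and plate layout are laboratory details that an article commonly leaves to the full protocol, so their absence is no finding in itself.

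The exposure is also narrow. The risk stratification aim does not use cytokine change, and a uniform shift leaves the ranking of patients within a phase unchanged.

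What these objections do not remove is that -20°C is a stated choice, that the draws are at least about 34 weeks apart, and that the design has no means of separating a systematic measurement shift from a programme effect.

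**Conclusion.** The point holds as a worthwhile, low-cost improvement and not as a demonstrated error. The interval of about 8 months follows from the article's own schedule; the extension to about 12 months is conditional. Within a single uncontrolled cohort, a storage effect (if all samples are assayed at the end) or a run effect (if each phase has its own run) cannot be excluded from the phase 1 to phase 3 comparison of IL-6, TNF-alpha and IL-10.

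The size is unknown and may be zero. On assumed losses of 0, 0.5, 1 and 2% per month, an end-of-study assay would show an apparent rise of 0, 4, 8 and 17% over 7.8 months. Cytokine analyses within one phase are not directly affected.

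**What to change.** In section 2.9, store aliquots at -80°C and assay each patient's phase 1 and phase 3 samples side by side on the same plate. The shared plate removes the run difference from the within-patient change. It does not remove the age difference, so the colder storage is there to limit any loss.

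If only -20°C is available, use the same short storage time for both phases and calibrate runs with a common control pool on every plate. Do not rely on adjusting the phase comparison for plate: where plate and phase coincide, that adjustment removes the phase effect itself.

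The cost is freezer space and slightly more laboratory logistics. No extra blood, visits or patients are needed. The change has to be made before the first samples are stored, because loss in early samples cannot be repaired afterwards.
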